### Surveys

#### ANU-ADRI Tool

ANU-ADRI is an evidence-based 79-item risk assessment tool designed to predict the risk of future AD development. ANU-ADRI collects information on education, BMI, cholesterol, diabetes, history of traumatic brain injury, depression, physical activity, cognitive engagement, social network, fish intake, alcohol consumption, smoking, and pesticide exposure [11]. This valid and reliable tool will be used as the primary inclusion tool and a primary outcome variable in this study. Details of the ANU-ADRI scoring procedures are published elsewhere [11]. Briefly, scores for each subsection will be tallied and a composite risk score will be used for all the analyses. A change of 2 points in the ANU-ADRI score is considered clinically meaningful [41].

#### Anxiety

Anxiety will be assessed using the General Anxiety Disorder 7-item scale [42]. It is a valid and reliable measure of anxiety among older adults [43]. Scores range from 0 to 21, with higher scores indicating higher anxiety severity [42].

#### Loneliness

The University of California, Los Angeles, 3-item Loneliness Scale [44] will be used to determine the degree of loneliness among the study population. Scores range from 3 to 9, with higher scores being associated with greater levels of loneliness. Scores above 5 indicate loneliness.

#### Health-Related Quality of Life

Health-related quality of life will be measured using the 12-Item Short Form Health Survey, which is a valid and reliable measure of health-related quality of life in many study populations [45]. It is composed of 2 subscales: physical health and mental health. Scores range from 12 to 47, with higher scores indicating higher self-reported quality of life.

#### Perceived Stress

Perceived stress will be assessed using the Perceived Stress Scale [46]. Scores range from 0 to 40, with lower scores indicating lower perceived stress. Scores ranging from 0 to 13 indicate low stress, 14 to 26 indicate moderate stress, and >26 indicate high stress.

#### Physical Activity

Physical activity will be assessed using the International Physical Activity Questionnaire, which is the physical activity component of the ANU-ADRI. This survey is a valid and reliable self-report tool for quantifying moderate, vigorous, and sedentary behaviors [47]. The International Physical Activity Questionnaire specifically asks about the participant’s physical activity performed within the previous 7 days.

#### Health Care Use

The health care use form of the University of California at San Diego will be used to quantify how frequently the participants have visited their physician or used any form of health care within the previous 3 months. Higher values indicate more health care use during the time frame [48].

#### Sleep

Sleep quality will be assessed using the Pittsburgh Sleep Quality Index. This 9-item assessment produces a score ranging from 0 to 27, with higher scores indicating poorer sleep. Individuals scoring ≥5 are deemed poor sleepers [49,50].

#### Depression

Depression will be assessed using 2 surveys. The Patient Health Questionnaire is a 9-item questionnaire with scores ranging from 0 to 27. Higher scores indicate higher levels of depression [51]. The Center for Epidemiological Studies-Depression is a 20-item depression scale. Higher values indicate higher levels of depression, with a score ≥16 indicating individuals at risk for clinical depression. The Center for Epidemiological Studies-Depression is a part of the ANU-ADRI [11].

#### Everyday Cognition

The 12-item Everyday Cognition scale is a brief questionnaire designed to detect cognitive and functional decline. This scale has been shown to correlate with functional measures and neuropsychological scores in people with normal cognitive function, mild cognitive impairment (MCI), and AD [52].

#### Blood Biomarkers

Blood sample will be collected at each of the 4 study visits. High-sensitivity C-reactive protein, interleukin-6, and brain-derived neurotrophic factor will be analyzed by a third-party laboratory. Cholesterol (total, HDL, and LDL), triglycerides, and blood glucose levels will be analyzed in whole blood using a Cholestech LDX system (Abbott Laboratories). Whole blood will be collected in a 40 µL capillary tube, immediately transferred into a Cholestech cartridge, and analyzed. Cholestech LDX values are valid and reliable for the assessment of triglycerides, LDL, HDL, and total cholesterol [53]. APOE status will be analyzed at baseline only.

### Study Arms

#### Randomization

Before the recruitment of participants into the intervention, all the study ID numbers were randomly preassigned. A member of the research team assigned each study ID to a number generated by a random numbers table. As participants (who met all the inclusion criteria and none of the exclusion criteria and signed the informed consent form) were enrolled in the study, they were assigned a study ID number.

#### HC Intervention

The participants randomly allocated into the HC arm of the study will be assigned a personal health coach to work with for the duration of the study. HC will take place remotely through videoconferences and asynchronous chat messages and focus on helping the participants improve their brain health by working on the following lifestyle domains: nutrition, physical activity, sleep, stress, social engagement, and cognitive activity. HC will communicate with the participants about each of these modifiable risk factors and then tailor their recommendations and communications to the specific lifestyle areas needed for each participant. HC participants will also be provided access to a cognitive health app (Citruslabs), through which they can access cognitive training activities, workout routines, and recipes. HC is different from traditional interventions used in RCTs. Instead of testing a uniform program to fit all the participants, the HC recommendations and communications will be tailored by the coach to fit each participant’s unique needs.

The HC will actively reach out to participants 1-2 times per week through asynchronous messages and will provide articles on various lifestyle modifications, such as nutrition information and physical activity, based on the focus for each participant. In addition, the participants will have unlimited access to their coach to ask questions or obtain the coach’s recommendations. Meetings with the coach will be scheduled on a monthly basis through videoconference or phone to assess the progress toward the goals, discuss any barriers they have encountered, and strategize personalized ways to attain the goals. The lifestyle domains will be chosen based on a combination of the participant’s preferences and the coach’s recommendations. For example, if the HC identifies nutrition as the primary source of need for a participant but the participant is not ready to work on that area, the HC will make alternative recommendations to meet the participant where they feel ready to make a change.

The HC intervention is designed to support participants through the recommended lifestyle changes to improve brain health and reduce dementia risk. The topics that will be discussed during the initial intake session include (1) description of the HC process, (2) description of lifestyle domains and how they are related to brain health, (3) gathering information from the participant on which lifestyle domains they seek and are willing to improve, (4) assessing motivation and readiness for change, and (5) assisting the participant for creating a vision for their future, including appropriate goal-setting. Although the monthly follow-up coaching sessions can differ between participants, they will typically include (1) reassessing goals and making appropriate modifications to meet personal health goals and (2) supporting the participant in overcoming the challenges they meet throughout their personal journey.

#### HE Control

Participants randomly assigned to the HE control group will receive biweekly emails including information on how to change their lifestyle to improve their brain health. To independently evaluate the efficacy of the intervention, the same lifestyle domains will be covered in both arms of the study. These lifestyle domains include physical activity, dietary habits, sleep, stress, social engagement, and cognitive activity. Throughout the duration of the intervention, the participants will only have access to the study staff during their on-site testing sessions. After the intervention, the number of articles opened by the participant will be tallied to determine engagement from the control group.

### Participant Recruitment

Participants were recruited in northwest Arkansas using local radio, email, social media advertisements, and word of mouth. The participants who met all the inclusion criteria and none of the exclusion criteria were randomly assigned to one of the groups before any assessments were completed.

The goal sample size for this study is approximately 200 participants. This sample size is considered sufficient to achieve random assortment, which was validated after examining the baseline characteristics of both groups. Cross-sectional, between-group differences in the baseline ANU-ADRI scores will be assessed using analysis of variance (ANOVA). Longitudinal studies following cognitively intact older adults have documented a 0.8 RBANS standard score change (SD 13.8) over a 12-month period [54]. Owing to the younger and wider age range to be recruited, we conservatively estimated a 1.75 standard score change with a comparable SD 10 among the control participants. In a 12-month pilot study of a similar intervention, a 5.8 (SD 7.4) standard score point increase on RBANS (ie, improvement) was found [55]. Assuming no additional improvement owing to a longer intervention, a sample size of 100 participants per group provides 80% power to detect a difference of 3.3 points between the intervention groups on the RBANS total index score (Cohen *d*=0.33) with an α of .05 and accounting for up to 20% attrition.

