**Results:**

Baseline characteristics indicate no difference between the intervention and control groups for AD risk (mean −1.68, SD 7.31; *P*=.90).

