### Statistical Analyses

Using the results of previous web-based intervention studies designed to reduce AD risk in an RCT design [11,56], a 2-point difference in the ANU-ADRI total score between the groups is expected over time [41]. A longitudinal observational study among adults demonstrated that a 1-point increase in ANU-ADRI score is associated with an 8% increase in the risk for developing MCI or dementia, mediated by brain volume, over the following 12 years [57]. A 2.5-point within-group change was found to be statistically significant in a web intervention [11]. Owing to the population health effects that are possible with a scalable remote intervention, these metrics are clinically and statistically meaningful at the individual and group levels.

Exploratory analyses will be performed on an intent-to-treat basis. One-way ANOVA will be used to compare the groups on functional fitness; biomarker measures; health-related variables; and digital, cognitive assessments at baseline. In addition, sex differences in baseline characteristics and change scores will be evaluated using a 2×2 (group and sex) ANOVA. Repeated measures ANOVA will be used to determine the differences over time between the groups. APOE status and the presence of homozygous E4 alleles will be used as a dichotomous variable and as a covariate for change in results after the intervention.

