**Figure 1 figure1:**
[figure not shown]
Participant screening and enrollment funnel.

**Table 2 table2:** Baseline characteristics (N=204).

Variables	Health education (n=101)	Health coaching (n=103)	Total (N=204)	*P* value^a^
Age (years), mean (SD)	61.4 (8.9)	62.4 (7.6)	61.9 (8.3)	.38
Sex (female), n (%)	77 (76.2)	75 (72.8)	152 (74.5)	—^b^
Ethnicity (White), n (%)	98 (97)	100 (97.1)	198 (97.1)	—
ANU-ADRI^c^ total, mean (SD)	−1.61 (7.34)	−1.75 (7.32)	−1.68 (7.31)	.90
ANU-ADRI risk, mean (SD)	8.97 (5.91)	8.41 (5.57)	8.68 (5.73)	.48
ANU-ADRI protective, mean (SD)	−10.38 (4.49)	−10.15 (4.60)	−10.26 (4.54)	.72

^a^Obtained from 2-tailed *t* test.

^b^No statistical analysis was performed.

^c^ANU-ADRI: Australian National University-Alzheimer Disease Risk Index.

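### The planned comparison does not name the outcome's own baseline value as a covariate, which probably costs power, and non-significant baseline comparisons are wrongly read as confirming the randomisation

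*Protocol article*

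**What the plan says.** Under Statistical Analyses, the protocol article assigns differences over time between the groups to a repeated measures ANOVA. Change scores appear in a 2×2 ANOVA by group and sex. APOE status is the one covariate named for change after the intervention. The baseline value of the outcome being analysed is not named, although Table 1 shows that ANU-ADRI and the other outcome measures are collected at baseline and at all three later visits.

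On baseline comparisons, Participant Recruitment states: "This sample size is considered sufficient to achieve random assortment, which was validated after examining the baseline characteristics of both groups". It also plans an ANOVA of baseline ANU-ADRI. Statistical Analyses adds further tests: "One-way ANOVA will be used to compare the groups on functional fitness; biomarker measures; health-related variables; and digital, cognitive assessments at baseline". The abstract reports: "Baseline characteristics indicate no difference between the intervention and control groups for AD risk", with P=.90. Table 2 gives the figures behind that statement, with a footnote on the P values: "Obtained from 2-tailed *t* test".

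Two points on ANU-ADRI is the protocol's own yardstick. The ANU-ADRI Tool section says: "A change of 2 points in the ANU-ADRI score is considered clinically meaningful", and Statistical Analyses expects a 2-point difference between the groups.

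**The concern.** There are two separate issues.

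**Precision.** When baseline is treated as the first level of the time factor, the group-by-time contrast from baseline to 24 months is the difference between arms in mean change. That gives the baseline value a fixed weight of 1. Regressing the follow-up value on baseline lets the data choose the weight, and under randomisation the residual variance is smaller whenever the correlation is below 1. The loss from not doing so falls on the primary outcome even if the arms are perfectly balanced.

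**Inference from baseline tests.** Under randomisation any baseline difference is due to chance, so the null hypothesis of a baseline test is true by design. A large P value therefore cannot confirm that allocation worked, and sample size does not produce randomness; the allocation procedure does. Chance imbalance matters through its actual size and its correlation with the outcome, not through its P value. Adjustment should therefore be fixed in advance and not depend on such a test.

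**Working it through.** **Inputs from the protocol article**
- Table 2, ANU-ADRI total, mean (SD): health education −1.61 (7.34), n=101; health coaching −1.75 (7.32), n=103; all −1.68 (7.31); P=.90.
- Participant Recruitment: 100 per group with up to 20% attrition, so 100 × 0.8 = 80 completers per arm; α = .05, taken as two-sided.
- ANU-ADRI Tool and Statistical Analyses: 2 points as the effect of interest.

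**Assumed, not in the document:** the correlation r between baseline and 24 months, taken as 0.5 to 0.8, and a follow-up SD equal to the baseline SD of 7.31.

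**Step 1. Reproduce the stated P value.**
- Pooled SD = √[(100×7.34² + 102×7.32²)/202] = 7.33.
- SE = 7.33 × √(1/101 + 1/103) = 1.026.
- Difference (education minus coaching) = −1.61 − (−1.75) = 0.14; t = 0.14/1.026 = 0.136 on 202 df; P = .89.
- A difference of 0.13, which the rounded means allow, gives P = .90. The stated value reproduces within rounding.

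**Step 2. Precision of the two analyses.**
- SD of change = 7.31 × √[2(1−r)].
- Residual SD after baseline adjustment = 7.31 × √(1−r²).
- SE of the group difference = SD × √(2/80).
- Power for 2 points comes from the noncentral t distribution on 158 df.

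| r (assumed) | SD, change | SD, adjusted | SE, change | SE, adjusted | Power, change | Power, adjusted |
|---|---|---|---|---|---|---|
| 0.5 | 7.31 | 6.33 | 1.156 | 1.001 | 41% | 51% |
| 0.6 | 6.54 | 5.85 | 1.034 | 0.925 | 49% | 58% |
| 0.7 | 5.66 | 5.22 | 0.895 | 0.825 | 60% | 67% |
| 0.8 | 4.62 | 4.39 | 0.731 | 0.693 | 78% | 82% |

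The variance ratio, change to adjusted, is 2(1−r)/(1−r²) = 2/(1+r). That is 1.33 at r=0.5 and 1.11 at r=0.8, so the change-score variance is 33% to 11% larger.

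**Step 3. What the realised imbalance implies.** Given a baseline imbalance D, a change-score comparison has conditional bias of size (1−r)D. With D = 0.14:
- r=0.5: 0.5 × 0.14 = 0.07 points
- r=0.8: 0.2 × 0.14 = 0.03 points

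Against the 2-point target these are 3.5% and 1.4%. The imbalance itself is 0.14/7.31 = 0.02 SD.

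**The case against.** The strongest reply is that the article is a condensed account. One sentence on repeated measures ANOVA does not settle how baseline enters, and the analysis plan, which is not shown, may already adjust for it. A comparison of change is also unbiased over repeated randomisations, so the choice concerns efficiency, not validity. The power figures compare a single-visit change score with a single-visit adjusted analysis, not the full multi-visit model, and rest on an assumed correlation and SD. All of this stands, and it limits the point to a recommended improvement. It does not remove it: the article does choose a model and does name a covariate, and the outcome's own baseline is not the one named. Nor would any analysis plan repair the published statements about baseline balance.

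Four stronger readings are tempting, and the document does not support them.
- *No baseline covariate is named.* APOE status is named, and Blood Biomarkers says it is analysed at baseline only. Sex is a factor in the change-score analysis.
- *The choice of model depends on the baseline tests.* Nothing in Participant Recruitment or Statistical Analyses makes it conditional on them.
- *The baseline test has about 49% power for 2 points, so an imbalance could have been missed.* The arithmetic is right for 101 against 103 participants, but it concerns a population difference that randomisation rules out. The imbalance that matters is the observed one, and it is known to be 0.14 points.
- *The primary comparison carries a bias of 1.0 to 0.4 points and a type I error of about 10% to 7%.* Those figures presuppose a 2-point imbalance in ANU-ADRI, which did not occur.

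It is also fair to note that the article refers to examining baseline characteristics generally, not only P values.

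**Conclusion.** The point holds as a matter of precision and of wording.

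If baseline is handled as one more visit, the primary comparison gives up about 10 percentage points of power at r=0.5 and about 4 at r=0.8 for a 2-point ANU-ADRI effect. This rests on 80 completers per arm, SD 7.31 at follow-up, the assumed correlations, and the single-visit comparison as a stand-in for the full model. It does not depend on any imbalance.

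The claims that random assortment was confirmed and that the arms do not differ are unsound as inferences, but for ANU-ADRI the effect is negligible: at most about 0.07 points of conditional bias for r of 0.5 or more, based on all participants at baseline. For RBANS, the biomarkers and functional fitness, Table 2 shows no baseline values by arm, so the size of any imbalance cannot be judged from this document. Baseline adjustment would cover those outcomes too.

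**What to change.** 1. In Statistical Analyses, model the follow-up values of ANU-ADRI, and of each secondary outcome, with that outcome's own baseline value as a covariate, whatever the baseline P value. If the analysis plan already does this, say so in the article.
2. Drop the planned baseline ANOVAs and the P value column of Table 2, and keep the descriptive summaries by arm.
3. In Participant Recruitment, remove the claim that sample size achieves, and baseline examination confirms, random assortment. State that the groups were formed by randomisation and that baseline values are described and adjusted for.
4. In the abstract, replace the statement of equality and its P value with the observed values: means of −1.61 and −1.75, a difference of 0.14 points.

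The cost is one degree of freedom per model and a few sentences. The baseline measurements are already collected, so no new data are needed.

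### The RBANS power statement uses an unsupported control SD of 10, and its 3.3-point difference does not have the stated 80% power

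*Protocol article*

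**What the plan says.** All the inputs are in the protocol article, under Participant Recruitment.

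- **Control source.** Longitudinal studies of cognitively intact older adults "have documented a 0.8 RBANS standard score change (SD 13.8) over a 12-month period".
- **Control assumption.** "Owing to the younger and wider age range to be recruited", the authors write, "we conservatively estimated a 1.75 standard score change with a comparable SD 10 among the control participants".
- **Intervention source.** In a 12-month pilot of a similar intervention, "a 5.8 (SD 7.4) standard score point increase on RBANS (ie, improvement) was found".
- **Carry-over to two years.** "Assuming no additional improvement owing to a longer intervention", so the intervention mean stays at 5.8.
- **Power claim.** "a sample size of 100 participants per group provides 80% power to detect a difference of 3.3 points" on the RBANS total index score. This is given as Cohen d = 0.33 at α = .05, with allowance for up to 20% attrition.

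The paragraph gives no derivation of the SD of 10 or of the 3.3 points. The Abstract lists RBANS among the secondary outcomes. The primary outcome is the ANU-ADRI.

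**The concern.** Two things in the paragraph do not hold together.

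First, the only control-type SD cited is 13.8, and the plan works with 10. Detectable differences are proportional to the SD, so the substitution makes the trial look more sensitive. The reason offered is the age range. A wider range does not suggest a smaller spread, and what a younger sample would do to the SD is not argued.

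Second, 3.3 points has no visible origin. It is not the difference between the planning means. If it is meant as a detectable difference, it should follow from the SD, n, α and power given in the same sentence, and it does not.

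This is the only power calculation in the article, and it supports the aim on cognitive decline. If it stands uncorrected, a null RBANS result could be read as coming from a comparison with 80% power for 3.3 points.

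**Working it through.** **Inputs** (all from Participant Recruitment): control change 1.75, SD 10; cited control-type SD 13.8; intervention change 5.8, SD 7.4; difference 3.3; d = 0.33; 100 per group; attrition up to 20%, so 100 × 0.8 = 80 completers per group; α = .05. Sidedness is not stated, so two-sided is assumed and one-sided is also shown. Power is from the noncentral t distribution for two independent means.

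**1. Size of the SD change.** (13.8 − 10)/13.8 = 27.5%. In variance terms, (13.8/10)² = 1.90.

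**2. SD behind the stated d.** 3.3/0.33 = 10, so the power sentence uses SD 10.

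**3. Reproducing the stated 80%.** With d = 0.33:

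| Completers per group | Two-sided power | One-sided power |
|---|---|---|
| 100 | 64% | 75% |
| 80 | 55% | 67% |

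None of these reaches 80%. The normal approximation for the n required is 2 × (1.960 + 0.842)²/0.33² ≈ 144.1, rounded up to 145. The t test gives 145.1, so 146 completers per group. Allowing for 20% attrition, 146/0.8 = 182.5, so 183 enrolled per group.

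**4. Difference implied by the means.** 5.8 − 1.75 = 4.05. Other readings give 5.8 − 0.8 = 5.0, or 5.8 + 1.75 = 7.55 if the control change is a decline. None gives 3.3.

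**5. Detectable difference and power across SDs.** With 80 completers per group, the 80% detectable standardised difference is 0.4457 (two-sided .05), so the detectable difference is 0.4457 × SD. Pooled SDs are √((a² + b²)/2):

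- SDs 10 and 7.4: √((100 + 54.76)/2) = 8.80
- SDs 13.8 and 7.4: √((190.44 + 54.76)/2) = 11.07

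| SD reading (control / intervention) | SD used | 80% detectable difference | Power for 4.05 | Power for 3.3 |
|---|---|---|---|---|
| 10 / 7.4 | 8.80 | 3.9 | 82.5% | 65% |
| 10 / 10 | 10 | 4.5 | 72% | 55% |
| 13.8 / 7.4 | 11.07 | 4.9 | 63% | 47% |
| 13.8 / 13.8 | 13.8 | 6.2 | 45% | 32% |

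With 100 completers per group at SD 10, the detectable difference is 3.98.

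**6. A setting that does return 3.3.** With the pilot SD of 7.4 in both groups and 80 completers, 0.4457 × 7.4 = 3.30. But d would then be 3.3/7.4 = 0.45, not 0.33. The article does not say that 3.3 arose this way.

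**The case against.** Several points on the other side have weight.

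- **What the adverb modifies.** It applies most directly to the mean change of 1.75, which is cautious against 0.8 if both are gains. A reader might infer that the authors call the SD conservative; the sentence does not clearly say so. What remains is that 10 is called comparable to a cited 13.8.
- **SD 10 lies between the two cited SDs.** It is about 10% below their pooled value of 11.07, so it is not an extreme choice. It is still unsupported as a control SD, which is how the text presents it.
- **A detectable difference need not equal the expected one.** The wording presents 3.3 as detectable, and a target below 4.05 would be cautious in itself. So the mismatch with 4.05 alone does not prove an error. The failure is that 3.3 is not detectable with 80% power at the stated d and n.
- **The plan's own means and SDs give adequate power for 4.05.** With SDs 10 and 7.4, power for 4.05 points is 82.5% after attrition. A reader might infer from the 45% figure that the trial cannot detect its own expected RBANS effect. The article does not support that as a general statement, because 45% needs SD 13.8 in both groups and the only intervention SD cited is 7.4. With 13.8 in controls only, power is 63%.
- **Baseline adjustment could recover power.** At SD 10 with 80 per group, the normal approximation requires a correlation of about 0.67. The article states none, and the quoted SDs accompany changes.

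**Conclusion.** The power statement is wrong as written. At SD 10, which its own d implies, power for 3.3 points is about 64% with 100 per group and 55% with 80, against the stated 80%. This assumes a two-sided, unadjusted comparison of two means; a one-sided test does not reach 80% either (75% and 67%).

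The control SD of 10 is 27.5% below the only control-type value cited, favours power and has no stated source. Correcting the SD alone would not repair the sentence, because the difference, d, n and power already disagree at SD 10.

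The planning means imply 4.05 points. Power for that difference with 80 completers per group ranges from 82.5% to 45%, depending on which SDs hold, and the article does not settle which.

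The consequence is limited to how the cognitive aim is interpreted. A reader might infer that the trial as a whole is underpowered. This calculation does not show that, since it concerns a secondary outcome and says nothing about power for the ANU-ADRI.

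**What to change.** Reconcile difference, SD, d, n and power in one statement:

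1. Either restate the 80% detectable RBANS difference as about 4.5 points (SD 10, 80 completers per group, two-sided .05), or keep 3.3 points and restate its power as about 55%.
2. Say that the planning means imply 4.05 points, and keep that separate from the detectable difference.
3. Stop describing the SD of 10 as comparable to 13.8, or give its source.
4. Tabulate power and detectable difference for control SDs from 10 to 13.8, stating the intervention SD used in each row.

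If trial data are used to check the SD, use the blinded pooled SD of RBANS change, for example at 4 or 12 months. The baseline RBANS SD should not be substituted directly, because it is cross-sectional and the planning SDs accompany changes. With equal variances, SD of change = baseline SD × √(2(1 − r)), so the two agree only at r = 0.5. A baseline SD is usable only with an explicit baseline-to-follow-up correlation.

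The cost is revised wording and one table. Baseline testing is already complete for 204 participants, and no further enrolment is asked for.

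### The RBANS power statement is internally inconsistent: 80% power, 3.3 points, d=0.33, 100 per group and 20% attrition cannot all hold

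*Protocol article*

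**What the plan says.** The calculation is in Methods, Participant Recruitment. The target is set first: "The goal sample size for this study is approximately 200 participants". Three sets of figures for change in RBANS follow:

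- A longitudinal source in cognitively intact older adults "documented a 0.8 RBANS standard score change (SD 13.8) over a 12-month period".
- For planning, "we conservatively estimated a 1.75 standard score change with a comparable SD 10 among the control participants".
- In a 12-month pilot of a similar intervention, "a 5.8 (SD 7.4) standard score point increase on RBANS (ie, improvement) was found".

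The conclusion is that "100 participants per group provides 80% power to detect a difference of 3.3 points between the intervention groups on the RBANS total index score", given in parentheses as Cohen d 0.33, "with an α of .05 and accounting for up to 20% attrition". The section does not say which SD entered the calculation, whether the test is one- or two-sided, or whether a correlation between visits was assumed.

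The Abstract lists RBANS among the secondary outcomes; the primary outcome is ANU-ADRI. The Results section reports that enrolment ended with 204 participants.

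**The concern.** A difference, its standardised form, the number of completers and the power are tied together: once three are fixed, the fourth follows. Here all four are printed, and the power looks too high for the effect size beside it.

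The sentence matters because it is the article's only power calculation and supports the choice of about 200 participants. RBANS also serves the second aim, on cognitive decline. A reader who trusts the 80% would take a null RBANS result as fair evidence against a 3.3-point effect. If power is lower, that reading is too strong.

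**Working it through.** **Inputs** (all from Participant Recruitment): difference 3.3 points; d = 0.33; α = .05, taken as two-sided because sidedness is not stated; 100 per group enrolled; attrition 20%, so 100 × 0.8 = 80 completers per group; SDs 10 (control planning value), 7.4 (pilot) and 13.8 (longitudinal source).

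**SD implied by the printed d.** 3.3 / 0.33 = 10, which is the control planning value.

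**Formula.** For a two-group comparison of means with n per group, power ≈ Φ(d·√(n/2) − 1.96).

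**The plan's figure, using its own d.**
- n = 80: 0.33 × √40 = 2.087; 2.087 − 1.96 = 0.127; Φ(0.127) = 55.1%. The noncentral t gives 54.6%.
- n = 100 (attrition ignored): 0.33 × √50 = 2.333; 2.333 − 1.96 = 0.373; Φ(0.373) = 64.6%. The noncentral t gives 64.1%.
- One-sided (noncentral t): 66.8% at 80 per group and 75.2% at 100.

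None of these reaches 80%.

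**Power for 3.3 points under each SD in the section** (two-sided, noncentral t). The pooled SD is √((10² + 7.4²)/2) = 8.80.

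| SD used | d for 3.3 points | 80 per group | 100 per group |
|---|---|---|---|
| 7.4 in both arms | 0.446 | 80.0% | 88.1% |
| 8.80 (pooled 10 and 7.4) | 0.375 | 65.5% | 75.2% |
| 10 in both arms | 0.330 | 54.6% | 64.1% |
| 13.8 in both arms | 0.239 | 32.4% | 39.1% |

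Only SD 7.4 with 80 completers returns 80%. Working backwards under that SD, n = 2 × (1.96 + 0.842)² × (7.4/3.3)² = 79 completers per group, and 79 / 0.8 = 99 enrolled. So SD 7.4 reproduces the difference, the power, the sample size and the attrition allowance together, but not the printed d.

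**What d = 0.33 would require.** n = 2 × (1.96 + 0.842)² / 0.33² = 145 completers per group (146 by noncentral t), or 145 / 0.8 = 182 enrolled per group.

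**What 80 completers per group can detect at SD 10.** (1.96 + 0.842) × 10 × √(2/80) = 4.43 points (4.46 by noncentral t), a d of about 0.45.

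**Correlation needed to rescue the sentence.** If SD 10 were the SD of the score and the analysis adjusted for baseline, the variance would have to shrink by (3.3/4.43)² = 0.555. Setting 1 − r² = 0.555 gives r of about 0.67.

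**The case against.** Four arguments can be made for the plan.

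1. **The power may be right and the label wrong.** If SD 7.4 was meant for both arms, 80% for 3.3 points is correct and only d needs changing, to about 0.45. This stands as a possibility, and it is why 55% should not be presented as the true power. The sentence would still be wrong as printed, and SD 7.4 in both arms sets aside the SD of 10 that the same paragraph adopts for controls.

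2. **The analysis is not a plain two-sample test.** Statistical Analyses plans repeated measures ANOVA, and RBANS is measured at four visits. A suitable correlation could raise power. However, no correlation is stated, and SD 10 is attached to a score change, so any gain from subtracting baseline is already in it. The RBANS reliability of .81 quoted under RBANS Test Battery is not presented as a correlation between study visits over 24 months. The point limits how firmly 55% can be asserted but does not make the printed figures agree.

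3. **The expected effect is larger than 3.3.** If the control change is a gain, the plan's figures imply 5.8 − 1.75 = 4.05 points. With 80 per group, power for 4.05 is 72.1% at SD 10 and 82.5% at the pooled SD. A reader might infer from the 55% that RBANS has only a coin-flip chance of showing the effect the investigators expect; these figures do not support that. But the 80% is claimed for 3.3 points and d = 0.33, so the claim itself is not rescued.

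4. **It is a secondary outcome and enrolment is complete.** Both are true. They limit the consequence to how the RBANS result is justified and interpreted.

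**Conclusion.** The inconsistency is established: at 100 per group with 20% attrition, a two-group comparison cannot have 80% power for 3.3 points and also d = 0.33. Power for 3.3 points is about 55% with SD 10 in both arms, about 65% with the plan's two SDs pooled, and 80% with SD 7.4 in both arms. These values assume a two-sided α of .05, 80 completers per group, and no further gain from covariates or repeated visits.

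Two stronger readings are tempting but unsupported. One is that the authors mixed two SDs. The numerical match is close, but the article never says which SD was used, so this remains an inference. The other is that the trial as a whole is underpowered. The calculation concerns RBANS and says nothing about power for the primary ANU-ADRI outcome.

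The sentence should be corrected, and a null RBANS result should not be interpreted as if power for 3.3 points were 80%.

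**What to change.** Restate the sentence with one declared SD and the d and power that follow from it. For example: *With SD 10 and 80 completers per group, the trial has 80% power (two-sided α .05) for a difference of about 4.5 RBANS points (d = 0.45); power for 3.3 points is about 55%, or about 65% with a pooled SD of 8.8.*

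If SD 7.4 was intended for both arms, keep the 80%, correct d to 0.45, and explain why the control value of 10 was not used. If a baseline-adjusted or repeated-measures calculation was used, say so, state whether SD 10 is the SD of the score or of the change, and give the assumed correlation (about 0.67 is needed for baseline adjustment if it is the SD of the score).

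The cost is one corrected sentence. No extra participants and no change to trial conduct are needed. Unless SD 7.4 in both arms or an adjusted calculation can be justified, the stated power becomes less favourable.
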